#### **7.3.1.3 Secondary outcomes analysis**

We will repeat the analyses described above for the percentage of patients achieving the minimal important change on the MSK-HQ (using multilevel repeated measures logistic regression models) and for the secondary outcomes, including pain interference, and work productivity (WPAI-modified version). For the monthly pain intensity outcome, our models will include all follow-up responses.

#### **7.3.1.4 Sensitivity analysis**

The advantage of using multilevel repeated measures models is that all baseline responders can be included in the analysis even if they do not respond at one or more follow-up points. However, for patients responding at baseline but not at 3 or 6 months, we will also use multiple imputation including baseline and monthly measures (where available) to impute 3- and 6-month follow-up MSK-HQ scores and repeat the analyses above.

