## 7 STATISTICS AND DATA ANALYSIS

### 7.1. Sample size calculation

#### 7.1.1. Patient self-reported outcomes (primary objective 2.1.1.)

We anticipate from previous studies and discussions with GP colleagues that the level of practice engagement may wain if the recruitment period extends much beyond 3 months.

The median registered population size of general practices in North Staffordshire & Stoke-on-Trent is 7300. Assuming 80% are aged 18 and over and an annual consultation prevalence for musculoskeletal pain of 15%[33], then there will be 876 patients consulting for musculoskeletal pain on average per practice each year. Across 26 practices (2 per PCN), there will be 5694 eligible patients presenting in the 3-month recruitment period. Assuming a 25% response at baseline and 50% at follow-up, then there will be 1424 baseline responders (1139 (80%) consenting to further contact and record linkages) and 569 responders at 6-month follow-up (**Figure 1**).

**Figure 1.** Estimated number of patients recruited and followed up for the patient-reported outcomes subcohort (NB 3-month period of recruitment per practice).

[figure not shown]

The baseline response of 1424 will allow us to detect a difference of 3 or more points on the MSK-HQ (assuming standard deviation of 10) with 90% power at the 5% significance level for groups defined by a dichotomous covariate with prevalence of 10% (for example ethnicity: black, Asian, and ethnic minority patients vs white).

569 responders at 6-month follow-up will also allow us to detect a difference on the follow-up MSK-HQ of 3 or more points (assuming standard deviation of 10), with 80% power at the 5% significance level, for groups defined by a dichotomous covariate. This is based on a covariate with a prevalence of 10%, 2 follow-up time points (3m and 6m), adjustment for baseline MSK-HQ score, and assumed correlations of 0.5 between the two follow-up scores and between the follow-up and baseline

scores.[34] We will, however, use repeated measures multilevel models to ensure all patients responding at baseline can be included in the analysis.

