#### **7.3.1.2 Primary outcomes analysis**

We will report summary statistics (mean and standard deviation, median and interquartile range) for the MSK-HQ baseline, 3-month and 6-month score and its mean change over 3- months and 6- months overall and stratified by age, gender, and type of musculoskeletal pain. We will also determine the percentage of patients who achieve the minimal important change (MIC) for the MSK-HQ. This has been reported as 6 points, though varies by body region of pain. We will weight responses by age, gender, and type of musculoskeletal pain at baseline.

We will determine patient characteristics associated with baseline MSK-HQ score using multilevel linear regression models (patients nested within practices) including as covariates the key case-mix variables.

To assess inequalities in change in musculoskeletal health over the 6-months, we will use multilevel repeated measures linear regression models (follow-up measures nested within patients) to determine patients characteristics associated with MSK-HQ score at 3m and 6m, adjusting for baseline MSK-HQ score and the case-mix variables.

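### The MSK-HQ follow-up model does not include all baseline responders, as the protocol says it does: anyone missing both the 3- and 6-month scores drops out

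*Protocol*

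**What the plan says.** Section 7.3.1.2 of the protocol specifies the follow-up analysis for primary objective 2.1.1 as "multilevel repeated measures linear regression models (follow-up measures nested within patients"), used to find patient characteristics "associated with MSK-HQ score at 3m and 6m, adjusting for baseline MSK-HQ score and the case-mix variables". MSK-HQ is collected at 0, 3 and 6 months (Table 1), so this model has two possible outcome rows per patient. The same section presents the model as an assessment of inequality in how musculoskeletal health changes over the six months.

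Two other places describe who enters the model. Section 7.3.1.4 states its advantage: "all baseline responders can be included in the analysis even if they do not respond at one or more follow-up points". Section 7.1.1, after a power calculation on 569 responders, says: "We will, however, use repeated measures multilevel models to ensure all patients responding at baseline can be included in the analysis". Section 7.3.1.4 then adds multiple imputation of the 3- and 6-month scores for baseline responders without follow-up, as a sensitivity analysis.

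On numbers, section 7.1.1 expects "1424 baseline responders (1139 (80%) consenting to further contact and record linkages) and 569 responders at 6-month follow-up".

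**The concern.** A mixed model for repeated outcomes uses every patient who has at least one outcome value. It would use every baseline responder only if the baseline score were itself one of the outcomes. Here baseline is on the right-hand side, so the model retains patients who miss one of the two follow-ups but not those who miss both. With two MSK-HQ follow-ups, missing one or more includes missing both, so the sentence in section 7.3.1.4 is false for exactly the patients whose loss matters most.

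The study is about inequality, and section 6.2 names selective participation as a threat. If the main model is credited with covering everyone who answered at baseline, a reader may take the primary follow-up result as protected against attrition in a way that it is not. The analysis that does bring these patients back is ranked below it.

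**Working it through.** **1. The plan's own counts (section 7.1.1).** 7300 × 0.80 × 0.15 = 876 consulters per practice per year; × 3/12 = 219; × 26 practices = 5694. Then:

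- baseline responders: 5694 × 0.25 = 1423.5, stated as 1424
- contactable: 1423.5 × 0.80 = 1138.8, stated as 1139
- 6-month responders: 1138.8 × 0.50 = 569.4, stated as 569

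All three figures reproduce. The 50% therefore applies to the 1139, and 1424 − 1139 = 285 baseline responders cannot be followed up at all.

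**2. Who has an outcome row.** A patient enters the model with at least one of the 3- and 6-month scores. The number depends on the 3-month response and on its overlap with the 6-month response, and the protocol gives neither. Assuming 50% of the 1139 at each time:

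| Overlap of 3- and 6-month responders | Contribute | No outcome row, of 1139 | No outcome row, of 1424 |
|---|---|---|---|
| Same people both times | 1139 × 0.50 ≈ 569 | 570 (50%) | 570 + 285 = 855 (60%) |
| Independent | 1139 × 0.75 ≈ 854 | 285 (25%) | 285 + 285 = 570 (40%) |
| No overlap at all | 1139 | 0 (0%) | 285 (20%) |

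The last line is an arithmetic floor: it requires that nobody answers both times.

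**3. Check that these patients contribute nothing.** One data set of 1424 patients was simulated with a 10% group, SD 10, correlations of 0.5, 80% contactable and 50% independent response at each follow-up. In it, 823 patients had at least one follow-up score. The specified model was fitted to the full file and then to those 823 alone. Both fits used the same 823 patients and gave the same group estimate (−2.236) and standard error (1.005), as they must.

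**4. What the baseline-adjusted contrast estimates.** With equal SDs and the plan's correlation of 0.5, the slope on baseline is 0.5. If two groups differ by D at baseline and change by the same amount, the adjusted difference is (1 − 0.5) × D. For D = 3 points, the baseline difference that section 7.1.1 is powered to detect, this is 1.5 points with no difference in change. The contrast is a difference in follow-up score at a given baseline score, which is a legitimate quantity but not a difference in change.

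**5. Cost of moving baseline into the outcome instead.** Power for 3 points, two-sided 5%, 10% prevalence, 569 followed up; SD² is 100 times a variance factor:

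- baseline-adjusted: (1 + 0.5)/2 − 0.5² = 0.50, power about 86% (the protocol states 80% for 3 or more points)
- change, responders only: 0.50 + 0.25 = 0.75, about 70%
- change, with all 1424 baselines: 0.50 + 0.25 × 569/1424 = 0.60, about 79%

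**The case against.** Much can be said for the plan. It already intends to impute the missing 3- and 6-month scores using baseline and monthly measures. Objective 2.2.8 makes non-response bias a question in its own right. The follow-up power calculation uses 569 responders, so it does not depend on the disputed sentence. The separate baseline MSK-HQ model does use all baseline responders, and for monthly pain (section 7.3.1.3) anyone with a single reply enters, so the statement is much closer to true there. All of this stands, and it limits the consequences. It does not make the statement true for the MSK-HQ follow-up model.

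A reader might go further and infer that the primary estimate is biased. The documents do not support that. If missingness depends only on baseline MSK-HQ and the model covariates, the adjusted estimate from responders remains valid.

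A reader might also state a loss of 40% to 60% of baseline responders as the plan's figure. It is not one: it rests on an assumed 3-month response and overlap, and it counts the 285 who did not agree to further contact. The Study Summary sets the planned sample at 1,139, which excludes them, and section 6.3.2 leaves it unclear whether their answers are kept.

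Finally, a baseline gap of 6 points would turn equal change into a 3-point adjusted difference, the size the study targets. No 6-point gap appears in the documents, and objective 2.1.1 concerns reported outcomes, not change scores. Only the description of the model as assessing change needs correcting.

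**Conclusion.** The statements in sections 7.1.1 and 7.3.1.4 are wrong as written for the model in section 7.3.1.2. That follows from the model's form and needs no assumption. The main follow-up result rests on patients with at least one follow-up score.

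The size does need assumptions. With 50% response at each time, 25% to 50% of the 1139 contactable patients have no outcome row under independent to fully overlapping response, with a floor of 0%. On the base of all 1424, the full range is 20% to 60%. What is shown is a claimed protection that does not exist, not a biased estimate.

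**What to change.** 1. In sections 7.1.1 and 7.3.1.4, replace the claim by a statement that the model includes all patients with at least one follow-up score.
2. To meet the stated aim of including all baseline responders, make the already planned multiple imputation the main MSK-HQ follow-up analysis, with baseline measures, monthly pain scores and practice in the imputation model. Keep the baseline-adjusted model and its powered contrast as the analysis applied to the imputed data, and report the available-case model as the sensitivity analysis. The monthly pain scores matter here: imputing from the model's own covariates alone would add essentially nothing to the available-case result.
3. In section 7.3.1.2, describe the contrast as a difference in follow-up score conditional on baseline. A joint model of the 0-, 3- and 6-month scores with group-by-time terms may be added as a secondary analysis if change itself is of interest. Making it the main analysis would lower power from about 86% to about 79% under the plan's assumptions, so that is a trade-off and not required.

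The cost is a change of wording and slightly more analysis work. No data collection changes.

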### **7.3.2 EHR-only processes of care outcomes**

#### **7.3.2.1 Summary of baseline data**

We will determine the prevalence of patients consulting for a musculoskeletal pain condition and the percentage receiving each of the process of care outcomes (for example, strong opioid prescription) overall, and for each practice. We will stratify by musculoskeletal condition (for example, osteoarthritis, back pain, knee pain), age, and gender.

### **7.3.2.2 Primary outcomes analysis**

To determine each practice's case-mix adjusted percentage of patients receiving a process of care we will develop multivariable generalised logistic fixed effect regression models, with general practice as a fixed effect. We will first determine the association of process of care with the different case-mix factors. Each process of care (for example, strong opioid prescription) will be modelled separately, with the other processes of care included as case-mix variables in the model. We will use a backward stepwise selection process to determine which variables should be included in the final model. Those with a *p*-value of 0.20 or less will be retained. Using this model, the predicted probability of receiving the process of care for each consulting patient can be derived, based on the patient's characteristics and the model beta coefficient estimates. Each general practice's expected percentage receiving the process of care will then be determined by calculating the average predicted probability among all musculoskeletal consultants at that general practice. Comparison to the observed percentage indicates each general practice's absolute (observed - expected) and relative (observed/expected) deviation from the expected percentage receiving the process of care.

We will use funnel plots with 95% control limits to plot the case-mix adjusted deviation from the expected percentage across practices, and identify outlying practices. We will repeat the analyses for each 3- or 6-month interval from July 2016 and for specific musculoskeletal conditions (for example, osteoarthritis, back pain).

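### Section 7.3.2.2 does not take the practice term out of the expected percentage: read literally, expected equals observed in every practice, and the other reading leaves the intercept undefined

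*Protocol*

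**What the plan says.** Protocol section 7.3.2.2 sets out the adjusted analysis in a fixed order.

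1. The model is one of the "multivariable generalised logistic fixed effect regression models, with general practice as a fixed effect", built by backward selection in which variables with a p-value "of 0.20 or less will be retained".
2. Prediction: "Using this model, the predicted probability of receiving the process of care for each consulting patient can be derived", and this is "based on the patient's characteristics and the model beta coefficient estimates".
3. The expected percentage for a practice comes from "calculating the average predicted probability among all musculoskeletal consultants at that general practice".
4. Observed and expected are compared as "absolute (observed - expected) and relative (observed/expected) deviation from the expected percentage".
5. Display: "We will use funnel plots with 95% control limits to plot the case-mix adjusted deviation from the expected percentage across practices", with outlying practices identified from the plot.

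The section does not say that the practice coefficients are omitted, averaged or replaced at step 2. This is the only analysis listed under the primary outcomes heading for the EHR-only component, which serves objective 2.1.2 (the magnitude of between-practice variation). It is to be repeated for each 3- or 6-month interval from July 2016. Section 7.3.2.1 separately reports unadjusted percentages by practice.

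**The concern.** An expected percentage is useful in a funnel plot only if it says what an average practice would have recorded with the same patients. If the model behind it has its own free parameter for each practice, and that parameter enters the prediction, the expected value reproduces what the practice actually did. Observed minus expected is then zero by construction.

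The adjusted answer to a primary objective is at stake. So are the outlier work under objective 2.2.7 and the practice and PCN benchmarking under objective 2.2.5, which draw on the same kind of quantity. An analysis plan that follows this text faithfully inherits the problem.

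**Working it through.** **Inputs from the Protocol.** Section 7.1.1: median list size 7300, 80% adults, 15% annual consultation prevalence. Section 7.1.2: 26 practices, 6-month intervals.

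**The plan's own figure.** 7300 × 0.80 × 0.15 = 876 per practice per year; 876/4 = 219 per 3 months; 876/2 = 438 per 6 months; 26 × 438 = 11,388. This reproduces the stated total exactly, so the check uses 26 practices of 438 patients.

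**Algebra, literal reading.** Let the model be logit(p_i) = a_j + x_i'b for patient i in practice j. The maximum-likelihood score equation for a_j is Σ_{i in j}(y_i − p̂_i) = 0. Dividing by n_j, the mean prediction in practice j equals its observed proportion. Hence O − E = 0 and O/E = 1 in every practice, whatever other covariates are in the model.

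**Simulation.** These assumptions are not in the Protocol: three case-mix covariates, practice SD of 0, 0.3 or 0.5 on the logit scale, and a base-rate parameter of 10% or 30%. Limits are ±1.96 × √Σp̂(1−p̂)/n. The counts are practices out of 26 outside those limits, from one simulated dataset per row.

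| SD | Base | Raw practice % | Literal: max abs(O−E) | Literal: outside | Practice omitted: O−E, points | Practice omitted: outside | Average intercept: outside |
|---|---|---|---|---|---|---|---|
| 0 | 10% | 8.2–16.9 | 1.1e-15 | 0 | −2.6 to 3.0 | 1 | 1 |
| 0 | 30% | 28.8–39.7 | 6.7e-16 | 0 | −3.6 to 3.9 | 0 | 0 |
| 0.3 | 10% | 8.2–18.3 | 6.9e-16 | 0 | −6.4 to 4.5 | 8 | 7 |
| 0.3 | 30% | 24.0–43.6 | 7.8e-16 | 0 | −12.2 to 11.4 | 12 | 11 |
| 0.5 | 10% | 5.7–19.9 | 7.5e-16 | 0 | −8.4 to 8.7 | 13 | 14 |
| 0.5 | 30% | 17.8–49.3 | 5.6e-16 | 0 | −17.0 to 18.1 | 16 | 16 |

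In the last row, the highest practice recorded 0.493 × 438 ≈ 216 patients, and the literal procedure also expects 216. The lowest recorded 0.178 × 438 ≈ 78, and the procedure expects 78.

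The last column keeps practice as a fixed effect but predicts for everyone at the average practice intercept. It nearly matches omitting practice.

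**Backward selection does not help.** If practice is itself subject to the 0.20 threshold, its likelihood-ratio p-value was 7.6e-9 or smaller in the rows with SD 0.3 or more, so it stays in. At SD 0 it was 0.68 and 0.72, so it would be dropped where there is nothing to find.

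**The other reading: practice term excluded from the prediction.** The prediction then needs a common intercept, and none is stated. Under reference-cell coding, the software's intercept is that of the reference practice. Changing only that practice moved mean O/E over these ranges (SD and base rate assumed):

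- SD 0.2, base 30%: about 0.84 to 1.30
- SD 0.4, base 10%: about 0.56 to 2.83

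For deviations, one reference practice at SD 0.3 and base 30% gave −14.9 to +9.3 points, against −12.2 to +11.4 with practice omitted. The ordering is almost unaffected: the lowest rank correlation of O/E with the practice-omitted model was 0.995.

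**The case against.** The strongest reply is that the literal reading is not the intended one. The prediction is tied to patient characteristics, practice is not one of these, and comparing observed with expected makes sense only if practice is left out. That is a fair guess at intent, but the text does not say it, and it exchanges a null result for an undefined intercept. Either way the paragraph needs correcting.

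Several limits on the concern do stand, and a reader might otherwise infer more than the Protocol supports:

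- *That objective 2.1.2 would show no between-practice variation at all.* It would not. Section 7.3.2.1 reports unadjusted percentages for each practice, and the fitted practice coefficients carry the adjusted variation, although the plan does not use them. The null result is confined to the adjusted deviations and funnel plots.
- *That a fixed practice effect is itself the mistake.* It is not. With prediction from an average or recalibrated intercept it works, as the last column of the table shows.
- *That an arbitrary reference practice is built into the plan.* It arises only under reference-cell coding, and the Protocol states no coding. It shifts the level and the outlier calls, and it barely changes the ranking.

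The Protocol also mentions a separate statistical analysis plan, which is not shown, and intercept choice is often settled there. But this is not mere silence: the Protocol fixes the model, the prediction step and the deviation measure, and together these fail. Deviations of exactly zero would be noticed at once, so the error is likely to be caught. The repair would then be chosen after the data had been seen.

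**Conclusion.** The point holds for the procedure as worded. If the practice coefficients enter the predictions, O − E = 0 and O/E = 1 in every practice. This is an exact identity for unpenalised maximum likelihood and needs no assumption about the data. It does not hold exactly for random or penalised practice effects, which section 7.3.2.2 does not specify. If the coefficients are meant to be excluded, the expected percentage is not defined. Under reference-cell coding its level then depends on which practice is the reference, by an amount that rests on the assumed practice SD and base rate. Neither reading gives a usable adjusted measure of variation for this primary objective without a correction.

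**What to change.** State in section 7.3.2.2 that expected percentages contain no practice-specific term, and choose one of two routes:

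- fit the case-mix model without practice, in which case its overall intercept already makes total expected equal total observed; or
- keep practice effects, fixed or random, only to estimate the case-mix coefficients, and predict for all patients from one common intercept a*, solved so that Σ expit(a* + x_i'b̂) = Σ y_i.

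The recalibration in the second route matters: at the uncorrected average intercept, mean O/E was 1.01 to 1.13 in checks with assumed SD 0.2 to 0.5 and base 10% or 30%, against about 1.00 with practice omitted. If practice is kept, also say whether it is exempt from the backward selection.

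The cost is a few sentences in the Protocol, carried into the analysis plan. Data collection, sample size and practice burden are unchanged.

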| Primary                               | To estimate the magnitude and direction of differences between potentially 'disadvantaged' and 'advantaged' groups of patients in their reported musculoskeletal health outcomes up to 6 months after consultation [patient-reported outcomes/experiences subcohort]                                                                              | 
Expected main outcomes:
 
MSK-HQ score
 
Pain intensity (0-10 NRS)
 
Work productivity and activity impairment (WPAI)
                          |
|                                       | To estimate the magnitude of between-practice variation in processes of care for adults consulting with a MSK pain condition [EHR-only processes of care]                                                                                                                                                                                         | 
Expected main outcomes:
 
Practice-specific rates of primary care (re)consultation, secondary care referral, opioid prescribing, musculoskeletal imaging
 |

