## **2.1. Primary objectives**

**2.1.1.** To estimate the magnitude and direction of differences between potentially 'disadvantaged' and 'advantaged' groups of patients in their reported MSK health outcomes up to 6 months after consultation [patient-reported outcomes/experiences subcohort]

**2.1.2.** To estimate the magnitude of between-practice variation in rates of primary care (re)consultation, secondary care referral, opioid prescribing, and musculoskeletal imaging for adults consulting with a MSK pain condition [EHR-only processes of care]

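### Adjusting each process of care for the other processes, which are practice behaviour and main outcomes themselves, distorts the between-practice comparison that objective 2.1.2 needs

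*Protocol*

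**What the plan says.** Objective 2.1.2 in Protocol section 2.1 is "To estimate the magnitude of between-practice variation in rates of primary care (re)consultation, secondary care referral, opioid prescribing, and musculoskeletal imaging". The Study Summary lists the matching main outcomes as "Practice-specific rates of primary care (re)consultation, secondary care referral, opioid prescribing, musculoskeletal imaging".

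Section 7.3.2.2 sets out the analysis:

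- A logistic model is fitted for each process "with general practice as a fixed effect", and "with the other processes of care included as case-mix variables in the model".
- Covariates are then screened: "We will use a backward stepwise selection process to determine which variables should be included in the final model", with a retention threshold of p = 0.20.
- Each patient's predicted probability is "based on the patient's characteristics and the model beta coefficient estimates". The average of these over a practice's own patients is that practice's expected percentage.
- The outputs are observed minus expected (O−E), observed/expected (O/E) and outlier flags: "We will use funnel plots with 95% control limits to plot the case-mix adjusted deviation from the expected percentage across practices".

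Section 7.3.2.1 also reports, before any modelling, the "percentage receiving each of the process of care outcomes" for each practice. The section gives no reason for treating the other processes as case-mix, and it plans no model adjusted for patient factors alone.

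**The concern.** Case-mix adjustment should take out differences in who consults, so that what is left reflects what the practice does. Referral, imaging, prescribing and reconsultation belong to the second group. If they predict one another, a practice that refers and prescribes a lot has a higher expected imaging percentage because of its own referring and prescribing, and so looks closer to average on imaging. The same happens in turn for each of the other outcomes.

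Everything built on the expected percentage inherits this: the deviations, the outlier flags, the repeat analyses from July 2016 onwards, the benchmarks under objective 2.2.5 and the comparison of case-mix methods under objective 2.2.7. Section 11.1 plans reports back to participating practices, so a practice could be flagged, or not flagged, for reasons unrelated to its patients.

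**Working it through.** **Planning figure (section 7.1).** List size 7300, adult share 80%, annual consultation prevalence 15%: 7300 × 0.80 × 0.15 = 876 patients per practice per year. Then 876 / 4 = 219 in 3 months, 876 / 2 = 438 in 6 months, and 26 × 438 = 11,388. This reproduces the protocol's figure, and the point does not affect it.

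**Simulation of the section 7.3.2.2 procedure.** There were 26 practices of 438 patients and 60 runs per scenario. A logistic model with practice fixed effects was fitted, and the expected percentage was computed from patient covariates with a common intercept. (If the fitted practice effects entered the prediction, O−E would be zero for every practice, so they must be left out.) Two models were compared for one process: measured case-mix only, and measured case-mix plus the other three processes.

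The following are assumptions that the documents do not supply:

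- prevalences of 40%, 15%, 15% and 20%, with a 15% process as the outcome;
- practice-effect SD of 0.4 on the logit scale;
- correlation of practice effects across processes from −0.3 to 0.9;
- an unmeasured patient severity, balanced across practices, giving odds ratios between processes of about 1.0, 1.4 or 2.05.

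Backward selection was not simulated.

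The measure is the variance of O−E across practices less its mean sampling variance, as a ratio: adjusted for the other processes / case-mix only.

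| Odds ratio between processes | Corr. −0.3 | Corr. 0 | Corr. 0.5 | Corr. 0.9 |
|---|---|---|---|---|
| 1.0 | 1.00 | 1.00 | 1.01 | 1.01 |
| 1.4 | 1.13 | 1.01 | 0.82 | 0.66 |
| 2.05 | 1.27 | 1.08 | 0.71 | 0.39 |

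- **Processes unassociated:** no effect.
- **Associated, positively correlated practice effects:** the share removed is 1 − 0.82 = 18%, 1 − 0.71 = 29%, 1 − 0.66 = 34% and 1 − 0.39 = 61%.
- **Associated, independent practice effects:** inflation of 1% to 8%.
- **Associated, negatively correlated practice effects:** inflation of 13% to 27%.

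**Effect on flags at the strong end (odds ratio 2.05, correlation 0.9).** The SD of O−E falls from 5.6 to 3.8 percentage points. Flagged practices fall from 13.1 to 9.0 of 26, and about 5 change status. The correlation of O−E with the true practice effect falls from 0.94 to 0.85. With independent practice effects at the same odds ratio, the variance hardly moves, yet about 3 practices still change status.

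**Why the loss is partial.** With practice as a fixed effect, the coefficients for the other processes are estimated within practices. They shift the expected percentage only as far as processes go together among patients of the same practice.

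**The case against.** The best defence is that the other processes stand in for severity that the record does not hold. The EHR-only extract has no patient-reported severity, and section 6.2 aims to over-sample practices in deprived areas, so severity may well differ between practices. The simulation above assumes that it does not.

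When unmeasured severity is allowed to vary between practices (assumed SD of practice means 0.5 of the patient-level SD, effect 0.9 logit), adjusting for the other processes raises the correlation of O−E with the true practice effect. It goes from 0.63 to 0.74 with independent practice effects, and from 0.63 to 0.71 at a practice-effect correlation of 0.3. The gain largely disappears at 0.6, and at 0.9 the result is equal or slightly worse. This stands as a reason to keep such a model in view. It does not support making it the only adjusted analysis: the protocol does not offer this rationale, and the benefit also rests on correlations that are not given.

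Two further mitigations are real but incomplete. Crude practice percentages are reported under section 7.3.2.1, but they carry no model-based case-mix adjustment. Backward selection may drop some covariates, but with about 11,388 patients and a threshold of p = 0.20, the associated processes, which do the damage, will usually stay.

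A reader might infer that the variation is adjusted away altogether, or always biased downward. The documents support neither, because the fixed practice effect limits the loss and the sign depends on how practice styles correlate. A reader might also object that covariates can occur after the outcome in a 12-month window. Section 7.3.2.2 names no such window; 12 months is the follow-up length in the Study Summary and section 3, and covariate timing could be settled in an SAP.

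**Conclusion.** The point holds as over-adjustment. The protocol explicitly enters main outcomes of objective 2.1.2 as case-mix for one another and provides no analysis adjusted for patient factors alone. O−E, O/E and the outlier flags are distorted whenever processes are associated within practices.

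Where practice style is also shared across processes, part of the variation to be measured is removed: 18% to 61% of the variance for assumed practice-effect correlations of 0.5 to 0.9 and odds ratios of 1.4 to 2.05. There is no effect without association, and inflation of up to 27% when practice effects are negatively correlated. These figures rest on assumed correlations, prevalences and practice SD, and on severity being balanced across practices. Neither the direction nor the size in this study can be read from the protocol.

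**What to change.** In section 7.3.2.2, remove the clause on the other processes from the primary model. State that case-mix there is limited to patient characteristics known at or before the index consultation, for example age, sex, musculoskeletal condition, comorbidity, area deprivation, and earlier consultation or prescribing history. State also that the expected percentage leaves out the practice effect. Keep the model with the other processes as a labelled sensitivity analysis, and report how O−E and the flags change between the two.

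The cost is small: no new recruitment and one extra model per process. History before the index consultation can come from the extract that starts in July 2016 (section 6.4), although the earliest intervals will have little or none within it. The real downside is that some confounding by unrecorded severity may remain in the primary model. The sensitivity analysis indicates how much that could matter.
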